### Follow-up schedule

The overall follow-up schedule in this trial is shown in Table 1. Follow-up visits are conducted at each institution. We expect that regular follow-up visits will be scheduled every 4 weeks (± 7 days) to check the patients’ vital signs and to perform physical examinations. We will also evaluate disease progression by diagnostic imaging every 12 weeks, using X-ray, CT/MRI, or PDG-PET as scheduled. Blood tests are scheduled to be performed at 4 weeks and every 12 weeks thereafter (at the same time as diagnostic imaging). We will evaluate the primary outcome (i.e., the progression-free rate) at 48 weeks (Fig. 1). Adverse events and concomitant medications will be recorded through the trial.

### Sample size

We consider the progression-free rate at 48 weeks after treatment administration as the main outcome. We estimated the progression-free rates in the zaltoprofen (treatment) and placebo groups to be 80 and 30%, respectively. In the sample size calculation, we used the log-rank test to determine that 20 participants per group would be required for a 95% confidence interval and power of 90%. Thus, a total of 40 participants will be needed in this trial.

### Statistical analysis

The outcomes between the zaltoprofen treatment group and placebo group will be compared. Baseline characteristics will be described by means and standard deviations, or medians and quantiles (for continuous variables), and proportions (for categorical variables). The primary outcome will be analyzed based on the full analysis set (excluding participants who violate inclusion/exclusion criteria or do not take the study drugs), and will be compared between the groups at 48 weeks using the log-rank test. The secondary outcomes will also be compared between the groups at 24 and 48 weeks using *t*-tests, Mann-Whitney U tests, or Fisher’s exact tests. *P*-values less than 0.05 will be considered significant.

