### Randomization

We perform randomization at the time of trial registration (Fig. 1). One of the trial staff allocates participants to the two arms (1:1), one group receiving zaltoprofen and the other placebo. Randomization is performed by using a computer-generated random sequence with stratification for the size of tumor lesion and tumor location (i.e., knee or foot joints).

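### Allocation is stratified by tumour size and location, but the primary log-rank test is stated without strata: still valid, but conservative and slightly inefficient if those factors are prognostic

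*Protocol article*

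**What the plan says.** The Randomization section allocates 1:1 from a computer-generated sequence, with "stratification for the size of tumor lesion and tumor location"; location is split into knee and foot joints. It gives no cut-off or number of levels for size, and no expected effect of either factor on progression.

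Under Statistical analysis, the primary outcome in the full analysis set "will be compared between the groups at 48 weeks using the log-rank test", and P "values less than 0.05 will be considered significant". No strata or covariates are named for this test, and none are excluded.

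The Sample size section rests on the same test. It takes "progression-free rates in the zaltoprofen (treatment) and placebo groups to be 80 and 30%, respectively" and says that "we used the log-rank test to determine that 20 participants per group would be required", at 90% power. It does not mention strata either.

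**The concern.** Stratified allocation forces the arms to be alike on the chosen factors. If those factors influence progression, the true variance of the difference between arms becomes smaller than under simple randomisation. The ordinary log-rank variance takes no account of this. The statistic is then divided by too large a standard error, the real type I error falls below the nominal 5%, and some power is given away. A second loss comes from comparing patients of different risk within one risk set, which dilutes the treatment effect when the effect is proportional within strata.

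With 40 patients and about 18 expected events, it would be a pity not to use balance that the design has already secured. There is also a matter of pre-specification. With so few events the stratified and unstratified tests can give visibly different p-values, so it should be fixed in advance which one is primary.

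**Working it through.** **1. The plan's own figure.** Inputs from the Sample size section: 80% and 30% progression-free at 48 weeks, 90% power. Alpha is 0.05 (Statistical analysis); two-sided is my assumption.

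Two-proportion formula with mean rate 0.55: n = [1.960·√(2·0.55·0.45) + 1.282·√(0.8·0.2 + 0.3·0.7)]² / 0.5² = (1.379 + 0.780)² / 0.25 = 18.6, so 19 per arm.

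Under proportional hazards, HR = ln 0.8 / ln 0.3 = 0.185. Schoenfeld gives 15 events, or 15 / 0.45 / 2 ≈ 17 per arm. Freedman gives 23 events, or about 26 per arm. The stated 20 lies within this range and is accepted here. Expected events at 20 per arm: 20·0.2 + 20·0.7 = 18.

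**2. Unstratified against stratified test, balanced strata.** Assumptions that are not in the protocol: two levels of size by two of location, 10 patients per stratum allocated 5:5, exponential event times recorded on a 12-week grid (the imaging interval), no dropout, and baseline hazards set so that the overall 48-week rates equal the values shown. I ran 20,000 trials per cell. The Monte Carlo standard error is about 0.15 points for type I error and at most 0.35 for power. Entries are unstratified / stratified, in %.

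| Stratum hazards (assumed) | Type I, both arms 30% | Type I, both arms 55% | Power, 80% vs 30% (plan) | Power, 65% vs 30% (assumed) |
|---|---|---|---|---|
| 1/1/1/1 | 5.2 / 5.2 | 5.2 / 5.1 | 92.5 / 91.9 | 63.7 / 62.3 |
| 0.5/1/1/2 | 3.6 / 5.1 | 3.8 / 5.1 | 93.7 / 94.7 | 64.6 / 68.9 |
| 0.33/1/1/3 | 2.2 / 5.1 | 2.6 / 4.9 | 94.8 / 97.3 | 67.3 / 78.4 |

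Gain from stratifying at the planned rates: −0.6, +1.0 and +2.5 points. At 65% versus 30%: −1.4, +4.3 and +11.1 points. The 65% case implies 20·0.35 + 20·0.7 = 21 events, not 18.

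**3. A less tidy design.** Strata of random size (half large tumours, 40% foot or ankle), permuted blocks of 4 and 3,000 runs per cell, at the planned 80% versus 30%. A hazard ratio of 2 per factor corresponds to hazards 0.5/1/1/2, and 3 per factor to 0.33/1/1/3.

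| HR per factor (assumed) | Type I, unstratified / stratified | Power, unstratified / stratified |
|---|---|---|
| 1 | 4.5 / 4.7 | 92.0 / 91.2 |
| 1.5 | 5.5 / 5.6 | 92.9 / 92.7 |
| 2 | 4.1 / 5.6 | 93.9 / 95.0 |
| 3 | 2.5 / 3.9 | 94.3 / 96.6 |
| 5 | 1.1 / 4.4 | 95.6 / 99.0 |

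The standard error of a 5% rate over 3,000 runs is √(0.05·0.95/3000) = 0.4 points, so the 5.6% entries are compatible with 5%. The pattern matches step 2: little or no effect for weak factors, and clear conservatism from about HR 3 per factor.

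**The case against.** **The text is silent.** The article does not say that the strata will be ignored, and a condensed article may leave this to an analysis plan that is not shown. This stands as a limit. A reader might infer that the sponsor has decided to disregard the stratification; the documents do not support that. What can be said is that the primary test, its analysis set and its alpha are stated, and that the test as stated has no strata.

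**The effect depends on an unknown.** The protocol nowhere calls size or location prognostic and gives no effect for either. This also stands. At a hazard ratio of 1 to 1.5 per factor, the unstratified test holds its level and loses nothing. Making these the stratification factors suggests that the investigators think they matter, but it does not show how much.

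**Power is sufficient anyway.** At 80% versus 30% the unstratified test has about 92% power or more in every scenario examined. This stands too. A reader might take the 11-point loss as the loss for this trial, or conclude that the trial is underpowered for this reason. That figure belongs to an assumed 65% versus 30% combined with strongly prognostic factors, and neither is in the protocol. It shows only how the loss grows when the effect is smaller than planned.

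**Stratifying is not free.** With about 18 events spread over many small strata, information is lost where a stratum has patients from one arm only. This is true. With four strata the cost is about 1 point; with more levels it could be larger and the benefit smaller.

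**Conclusion.** The mismatch between stratified allocation and a primary test stated without strata is real, but it is minor. If the factors are prognostic, the unstratified test is conservative: two-sided type I error about 3.6 to 3.8% for stratum hazards 0.5/1/1/2 and about 2.2 to 2.6% for 0.33/1/1/3. The power given up is about 1 to 3 points at the planned rates, and about 4 to 11 points at an assumed 65% versus 30%. If the factors are not prognostic, nothing is lost by leaving them out.

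These sizes rest on assumed hazards, four strata, exponential times, no dropout and a two-sided 5% test. It would be wrong to infer that the planned test is invalid or inflates false positives; any departure from 5% is in the safe direction. Stratifying is an inexpensive gain in efficiency and clarity, and the trial's conclusion does not depend on it.

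**What to change.** Before unblinding, add one sentence to the analysis text: the primary log-rank test is stratified by tumour size and location, with the categories used in allocation. Estimate the hazard ratio from a Cox model stratified in the same way, and report the unstratified log-rank test as a sensitivity analysis. If the statistical analysis plan already says this, confirming it is enough.

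No extra patients or data are needed. The downside is about 1 to 2 points of power if the factors turn out not to be prognostic, and less benefit if allocation used many levels and the strata are sparse. The number of strata should therefore be checked before the sentence is fixed.

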### Outcomes

The primary outcome is the progression-free rate at 48 weeks after drug administration. Our definition of progression (exacerbation) is any serious event requiring surgical intervention. Exacerbation is indicated if a patient meets one of the following criteria:i).The joint circumference is increased by 2 cm or more with respect to the baseline (knee: 1 cm above patella; ankle joint: determined using the figure-eight method). If there is fluid accumulation, it is examined for the presence or absence of hematoma. An increase in joint circumference due simply to edema is not considered exacerbation.ii).The range of motion of the joint (i.e., active motion) is reduced by 20% or more with respect to the baseline (calculated by averaging three measurements with a goniometer).( i) or ii)must be detected in 2 consecutive evaluation periods conducted every 4 weeks)iii)An invasion of 5 mm or more of bone / cartilage erosion or a new lesion of bone / cartilage erosion of 5 mm or more, compared with that of baseline, is detected by computed tomography (CT) or magnetic resonance imaging (MRI).iv)An X-ray in the standing position shows the disappearance of joint space.v)An increase in the target lesion by 20% or more is determined by the response evaluation criteria in solid tumors (RECIST).( iii), iv) or v)must be detected once in any evaluation period conducted every 12 weeks).vi)Any surgical intervention for the disease that is performed for a specific reason.

We also evaluate secondary outcomes as follows:Progression-free rate (24 weeks and 48 weeks): Percentage of cases of complete response (CR), partial response (PR), and stable disease (SD, i.e., when CR and PR are unchanged for more than 4 weeks).Maximum Standardized Uptake Value (SUV) change by ^18^F-fluorodeoxyglucose- positron emission tomography (FDG-PET).Evaluation of affected limb function (baseline, 24 weeks, and 48 weeks): The Japanese Orthopedic Association score and Musculoskeletal Tumor Society (MSTS) score.Percentage of cases in which clinical benefit regarding pain, range of joint motion, and joint function compared with that of baseline is observed at 24 weeks and 48 weeks (judgment by investigators or clinical trial physicians).The types, incidence, and severity of adverse events and abnormal laboratory data (graded using common terminology criteria for adverse events (CTCAE) v4.0) will be assessed, evaluating the severity and relationship with the investigational drug (Fig. 1).

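### For the secondary 24- and 48-week progression-free percentages, Fisher's exact test is valid but runs at no more than about 2.5% true size with 20 per arm; Boschloo's exact test would recover about 5 to 10 points of power at almost no cost

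*Protocol article*

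**What the plan says.** The Outcomes section of the protocol article lists among the secondary outcomes "Progression-free rate (24 weeks and 48 weeks): Percentage of cases of complete response (CR), partial response (PR), and stable disease". Each patient is thus a yes or a no at each of the two times.

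The Statistical analysis section says that "The secondary outcomes will also be compared between the groups at 24 and 48 weeks using *t*-tests, Mann-Whitney U tests, or Fisher’s exact tests", with significance declared below 0.05. It does not match tests to outcomes one by one. The t-test and the Mann-Whitney test are for continuous or ordered data, so Fisher's exact test is left for a percentage.

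The primary outcome is handled differently: it "will be compared between the groups at 48 weeks using the log-rank test". The Sample size section bases 20 participants per group on that test, with this assumption: "We estimated the progression-free rates in the zaltoprofen (treatment) and placebo groups to be 80 and 30%, respectively".

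**The concern.** Fisher's test conditions on the total number of progressions. With 20 patients per arm, few distinct p-values are then attainable, and the test cannot get close to its nominal 5%. The unused part of the 5% is lost power. In a 40-patient trial of a rare tumour, that power cannot easily be regained by recruiting more patients.

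What is at stake is how the supporting evidence reads. A secondary progression-free rate that narrowly misses 0.05 next to a significant primary result could be taken as inconsistency, when part of the explanation is the test chosen. The effect is visible in single tables: 18/20 v 12/20 progression-free gives p = 0.065 by Fisher's test and p = 0.039 by Boschloo's test of the same hypothesis.

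**Working it through.** **Inputs.**
- 20 per arm, 1:1 allocation (Sample size, Randomization).
- Level 0.05 (Statistical analysis). Sidedness is not stated; two-sided is taken from the reference to a 95% confidence interval in Sample size.
- 48-week rates of 80% and 30% (Sample size). These are given for the primary outcome; applying them to the secondary one is an assumption.
- No 24-week rate is given, so one is derived below.

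**The plan's own figure.** Under constant hazards, the hazard ratio is ln(0.80)/ln(0.30) = 0.185. Simulated log-rank power (100,000 trials, no dropout) is 89.7% at 18 per arm, 91.1% at 19 and about 92.5% at 20. The smallest number reaching 90% is 19 per arm, so the stated 20 is reproduced to within one patient per arm.

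**24-week rates.** With h = -ln(S48)/48, S24 = exp(-24h) = √S48. This gives √0.80 = 0.894 and √0.30 = 0.548.

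**Size and power.** All 21 × 21 possible tables were enumerated. With R the set of tables that a test rejects,

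power(p1, p2) = Σ over (a, b) in R of Bin(a; 20, p1) × Bin(b; 20, p2),

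and size is the same sum with p1 = p2. Fisher's test rejects when its p-value is below 0.05. Boschloo's test uses Fisher's p-value as its statistic and sets the cut-off so that the largest size over all common rates stays within 5%. At 20 per arm, that means rejecting when Fisher's p is at most 0.0915.

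**True size.** Fisher's test: 2.0% to 2.5% at common rates of 30% to 80%, 1.2% at 90%, and at most 2.53% anywhere. Boschloo's test: at most 4.6% anywhere.

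**Power** (gains are taken before rounding):

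| Assumed rates | Fisher | Boschloo | Gain, points |
|---|---|---|---|
| 80% v 30% (48 weeks, plan's rates) | 84.6% | 90.1% | 5.5 |
| 89.4% v 54.8% (24 weeks, constant hazard) | 60.8% | 71.1% | 10.3 |
| 80% v 40% | 65.0% | 72.8% | 7.8 |
| 80% v 50% | 40.9% | 49.2% | 8.3 |
| 95% v 80% (progression rare) | 17% | 21% | 4.6 |

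The last three rows are assumed rates, chosen to show the range.

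**Borderline tables (progression-free counts).** 18/20 v 12/20: Fisher 0.065, Boschloo 0.039. 17/20 v 11/20: 0.082 and 0.042. 15/20 v 8/20: 0.054 and 0.030.

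**The case against.** The strongest reply is that nothing here is wrong. Fisher's test is standard at this sample size and controls the type I error. The trial is not powered on any secondary outcome, and the primary comparison and the sample size do not depend on this test. All of that stands, and it is why this is an improvement and not a correction. It can be added that several secondary outcomes are each tested at two times, so some conservatism does little harm. That has some force, but conservatism that happens to come from a coarse test is not a multiplicity rule. The article also lists three tests without assigning them, and the assignment may sit in an analysis plan that is not shown. Within the stated list, though, only Fisher's test fits a percentage.

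The power figures are conditional. The primary outcome counts six kinds of event, whereas the secondary one rests on response categories, so its rates may differ. If progression is rare, either test will usually be non-significant, and changing it would seldom alter the reading.

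Three stronger readings are tempting, and none is supported:
- A reader might infer that ignoring the time of progression is the main loss and that a log-rank analysis should be added. Log-rank power is about 92.5% at 48 weeks and 72% at 24 weeks, against 90.1% and 71.1% for Boschloo's test on the yes/no data. An uncorrected chi-square test gives 90.8% and 72.9%. Timing is therefore worth only about 0 to 2 points. A log-rank test would also answer a different question from the fixed-time percentage, and the primary analysis already compares progression by log-rank.
- A reader might quote the gap between Fisher's test and the log-rank test, about 8 and 11 to 12 points, as the cost. That overstates what a change of test for the same fixed-time question can recover.
- A reader might treat the 24-week rate as the only early comparison based on imaging. It is not: the change in maximum uptake on FDG-PET is also a secondary outcome, with a scan scheduled at week 24 in Table 1.

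**Conclusion.** The point holds as a modest matter of efficiency. With 20 per arm, the only listed test that suits the secondary progression-free percentages uses at most about half of its nominal 5%. A valid exact test of the same question would gain about 5.5 points at 48 weeks if the primary outcome's rates apply. It would gain about 10 at 24 weeks if hazards are also constant. Over the other rates tried, the gain is about 5 to 8 points. The size result needs only the 20 per arm and a two-sided 5% level; the power figures rest on the borrowed or assumed rates and on no missing outcomes. Neither the validity of the plan nor the primary conclusion is in question.

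**What to change.** In the Statistical analysis section, state that the secondary progression-free rates at 24 and 48 weeks will be compared with Boschloo's unconditional exact test (two-sided, 5%) in place of Fisher's exact test. The same test may optionally be named for the other two-group percentages. Make the change before unblinding.

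The cost is one sentence, with no new data, visits or patients. The outcome and the fixed time points stay as they are, the 5% level is held, and Boschloo's test is never less powerful than Fisher's. The one drawback is that readers know it less well, so a short description should accompany it.

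### The secondary outcomes are compared by tests that adjust for neither baseline nor the stratification factors, and within them pain and motion appear only as a judged yes/no benefit: valid, but less efficient than the collected data allow

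*Protocol article*

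**What the plan says.** All references are to the protocol article.

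- **Statistical analysis.** "The secondary outcomes will also be compared between the groups at 24 and 48 weeks using" three named tests: the t-test, the Mann-Whitney U test and Fisher's exact test ("Mann-Whitney U tests, or" Fisher closes the list). On the threshold, "values less than 0.05 will be considered significant". No covariate or model is named.
- **Outcomes, secondary.** JOA and MSTS scores come under "Evaluation of affected limb function (baseline, 24 weeks, and 48 weeks"). The FDG-PET outcome is worded as a change in maximum SUV. Pain, joint motion and joint function also form a proportion of patients with clinical benefit relative to baseline, decided by "judgment by investigators or clinical trial physicians", with no numerical threshold.
- **Outcomes, primary.** Criterion ii uses active range of motion, the mean of three goniometer readings, with a 20% reduction from baseline as the cut.
- **Table 1.** VAS, joint findings and joint function are mandatory at screening, before the first dose and every 4 weeks to week 48. FDG-PET is mandatory at screening and at weeks 24 and 48.
- **Randomization.** Allocation is 1:1, stratified by tumour size and by location.

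**The concern.** With 20 patients per arm, a baseline measurement that predicts the follow-up value removes part of the outcome variance at no cost. The named tests cannot use it as a covariate, and they leave out the two factors that stratified the randomization.

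No secondary outcome analyses VAS or goniometer values as measurements. For pain and motion, the secondary results will be a count of patients judged to have benefited, against an unstated threshold. A graded scale then becomes a yes/no answer, and readers will not learn how large any difference in pain or motion was.

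What is at stake is the precision and interpretability of the secondary results in a small trial. The primary result is not at stake.

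**Working it through.** **1. The plan's own figure.** The Sample size section states: "We estimated the progression-free rates in the zaltoprofen (treatment) and placebo groups to be 80 and 30%, respectively". It adds: "In the sample size calculation, we used the log-rank test", and concludes that "20 participants per group would be required for a 95% confidence interval and power of 90" per cent. At two-sided 0.05 and 90% power, a two-proportion formula gives 19 per group. A simulated log-rank test (exponential times, censoring at 48 weeks, 4,000 runs) has 92.6% power at 20 per group. So 20 per group reproduces, and it is used below. It was set for the primary outcome only.

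**2. Inputs for the secondary scores.**
- n = 20 per arm (Sample size).
- α = 0.05. Sidedness is not stated; two-sided is taken, consistent with the 95% interval in the Sample size section.
- Effect d in SD units and baseline-to-follow-up correlation r: the article gives neither. Assumed d = 0.8, and r = 0.3, 0.5 and 0.7.

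**3. Residual variance, relative to the follow-up variance** (equal variances at both times).
- t-test on follow-up values: 1.
- t-test on changes: 2(1 − r) = 1.40, 1.00, 0.60.
- ANCOVA on baseline: 1 − r² = 0.91, 0.75, 0.51.

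The ratio of ANCOVA to change-score variance is (1 + r)/2 = 0.65, 0.75, 0.85. ANCOVA is thus never less efficient than the change score, apart from one degree of freedom. The change score is worse than the follow-up value when r < 0.5.

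**4. Power from the noncentral t.** Noncentrality is d × √(n/2) / √(variance factor), with 0.8 × √10 = 2.53. Degrees of freedom are 38 for the t-tests and 37 for ANCOVA.

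| r | follow-up t-test | change t-test | ANCOVA | gain over the better t-test |
|---|---|---|---|---|
| 0.3 | 69% (2.53) | 55% (2.53/√1.40 = 2.14) | 73% (2.53/√0.91 = 2.65) | 4 points |
| 0.5 | 69% (2.53) | 69% (2.53/√1.00 = 2.53) | 81% (2.53/√0.75 = 2.92) | 12 points |
| 0.7 | 69% (2.53) | 89% (2.53/√0.60 = 3.27) | 93% (2.53/√0.51 = 3.54) | 4 points |

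Adding two binary stratification factors (35 degrees of freedom) costs about 0.1 percentage point, before any gain if they are prognostic.

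**5. Sensitivity to d, at r = 0.5.** For d = 0.6: t-test 46%, ANCOVA 57%. For d = 1.0: 87% and 94%. The ordering is the same.

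**6. Fewer evaluable patients at week 48.** The planning rates imply 0.80 × 20 = 16 and 0.30 × 20 = 6 progression-free patients. If no score were available after progression (an assumed extreme case), the standard error factor is √(1/16 + 1/6) = 0.479. The follow-up t-test then has noncentrality 0.8/0.479 = 1.67 on 20 degrees of freedom, power 36%. ANCOVA at r = 0.5 has 1.67/√0.75 = 1.93 on 19 degrees of freedom, power 45%. ANCOVA keeps its advantage, but both powers are low.

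**The case against.** **The planned tests are valid.** This stands. Under randomization, unadjusted t and rank tests hold their type I error, and chance imbalance is reflected in the standard error. The point is efficiency, not error.

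**Baseline may already be used.** This stands in part. A reader might infer that chance baseline imbalance passes undiminished into every secondary estimate. The article does not support that: the SUV outcome is already a change, the benefit judgement is made relative to baseline, and for JOA and MSTS the article does not say whether follow-up values or changes are tested. That is why both unadjusted tests appear in the table.

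**Motion is measured objectively elsewhere.** This stands. A reader might infer that motion enters the trial only through a physician's opinion. Primary criterion ii uses goniometer readings with a 20% cut. The point concerns the secondary outcomes only.

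**The yes/no judgement cannot be given a power.** This stands. Cutting one continuous measure at its midpoint and applying Fisher's exact test gives 36% power at d = 0.8. But that models a split of a single scale, not a physician's judgement across pain, motion and function, so it is not a figure for this endpoint. Nor can bias be inferred, since the trial is double-blind.

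**Covariates can be left to an analysis plan.** This stands only in part. The article does not leave the method open; it names three tests, and none takes a covariate.

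**ANCOVA does not solve missing scores.** This stands. It neither restores values missing after progression nor corrects selection by progression. Table 1's footnotes waive some assessments at withdrawal and at 4 weeks after the last dose once progression is detected or later treatment has begun.

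**Conclusion.** The point holds as a worthwhile improvement to the secondary analyses. The named tests leave out baseline and stratification information that the trial collects, and pain and motion have no continuous secondary analysis although both are measured.

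At d = 0.8 with 20 evaluable per arm, ANCOVA gains about 4 to 12 percentage points of power over whichever unadjusted t-test is better at that correlation. The advantage over a poorly chosen one is larger: 93% against 69% for follow-up values at r = 0.7, and 73% against 55% for changes at r = 0.3. Because r is not known in advance, a practical merit of ANCOVA is that the choice between the two need not be made.

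These sizes rest on assumed d and r and on complete data; week 48 power will be lower if scores are missing after progression. A reader might go further and infer invalid tests, biased judgement or a weakened primary result. The article supports none of these: the primary analysis and the sample size do not change.

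**What to change.** In the Statistical analysis section:

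- Analyse JOA, MSTS and SUVmax at weeks 24 and 48 by ANCOVA, with the baseline value and the two stratification factors (tumour size and location) as covariates.
- In Outcomes, add pain VAS and goniometer range of motion at weeks 24 and 48 as continuous secondary outcomes, analysed in the same way.
- Keep the investigator-judged benefit proportion as a supportive outcome.

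Fix the wording before unblinding, so that the choice of analysis cannot depend on the results. The cost is wording only: no new visits, measurements or patients. The change does not by itself deal with scores missing after progression.
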